### Study population

3.3.

The study will include 100 neonates (50 subjects and 50 controls).
•Neonates with gestational age ≥35, who experienced an episode of perinatal ischaemia and who were qualified for hypothermia treatment according to the Standards of Medical care of Neonates in Poland will be enrolled to the subject group (T) (Table 5)•Healthy, term neonates, who underwent echocardiography on days 3–7 of life (after closure of ductus arteriosus, or with trace, insignificant haemodynamic ductus arteriosus) for reasons such as difficult adaptation, gestational diabetes of the mother etc.

**Table 5 T5:** Indications for hypothermic treatment according to the standards of medical care of neonates in Poland 2021 (3).

Indications for TH		
Criteria Group A. Neonates born at ≥35 weeks of gestation, who experienced a period of hypoxia and at at least one of the factors in each of the sub-groups		Group B-neurological criteria. Neonates fullfilling the criteria of group with A with fluctuating states of consciousness who has at least one of the following factors:
Sub-group 1	Sub-group 2	– Hypotonia – Abnormal response to stimuli, including abnormal occulomoor or pupillary reflexes – Absent or weak sucking reflex – Clinically confirmed convulsions
– Apgar score ≤5 week 1, 3, 5, 10 min after birth – Continuous resuscitation with tracheal or mask withinn 10 min after birth	– Cord blood or blood pH within 1 h of life ≤7, however, with specicif assesment of pH results in the region of 7.01–7.15 – A BE base deficiency of at least 16 mmol/l cord blood or other samoles samples within 60 min after birth.	

Enrolment of patients will be based on patient medical records. Physicians responsible for recruitment of patients will gather additional information associated with the inclusion and exclusion criteria (Table 6) through detailed history, taking into account the clinical condition of patients and the results of tests. The study procedure will be explained to patient's guardians who will also receive an information leaflet. Guardians will then be asked to provide two copies of informed consent. Consent forms and information papers will be provided solely in the Polish language.

**Table 6 T6:** Inclusion and exclusion criteria.

Inclusion criteria (subjects)	Exclusion criteria

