### Echocardiographic examination

3.4.

All cardiac scans will be performed in standard echocardiographic projections with the aid of a sector probe with high frequency 8–12 MHz on a Philips camera. Echocardiography will be performed with continuous electrocardiography (ECG) recording from an ultrasound apparatus. Heart rate (HR) will be recorded. Doppler examination of the cerebral, renal and visceral circulation is an essential examination to assess haemodynamics and is routinely performed in ill neonates.

The scans will be saved as video recordings on storage media. In order to decrease the duration of patient examination to a minimum of 10–15 min, echocardiographic measurements will be performed on the recorded film clips or in the Image Arena echocardiographic program.

All parameters will be measured during end expiration and three consecutive cardiac cycles will be measured and averaged for each measurement.

LV and RV systolic and diastolic function on cardiac echocardiography will be assessed using the following imaging options (11–13):

3.4.A.

Pulse Doppler, M-mode, Tissue Doppler (TDI) (14). The examined parameters will also be determined by the tissue efficiency index, the so-called Tei-MPI index-Myocardial Performance Index, (in pulse and tissue Doppler option, cardiac output (left ventricular output) CO (LVOT), mitral valve (MV) early diastolic velocity/late diastolic velocity (*E*/*A*) ratio. MV *E*′/*A*′ ratio, SVC (CO), peak systolic velocity (*S*′), *E*′, *A*′, tricuspid valve (TV) early diastolic velocity/late diastolic velocity (*E*/*A*) ratio. TV *E*′/*A*′ ratio, tricuspidal annular plane systolic excursion (TAPSE), mitral annular plane systolic excursion (MAPSE), ductus arterious (DA) evaluation, tricuspidal valve regurgitation (rTV):

3.4.1A.

Two-dimensional (2D) M-mode measurements will be obtained from a parasternal long-axis view. The following measurements will be assessed: aortic diameter (AO) at the level of the valvular annulus, LV internal diameter at end diastole (LVIDd) and at end systole (LVIDs), left atrial size, RV diameter at end diastole (RVDd), and LV posterior wall thickness at end systole (LVPWs) and at end diastole (LVPWd). Fractional shortening (FS) will be calculated (LVIDd − LVIDs)/LVIDd × 100. The ECG will be recorded continuously during the examination.

3.4.2A.

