### The authors classified the parameters into the following groups depending on the evaluation of the function.

3.5.

•LV function: global LV function-MPI (PD, TDI), systolic function-FS%, LVO, *S*′, MAPSE, diastolic function-*E*:*A* ratio, *E*′:*A*′ ratio measured on MV.•RV function: global RV function-MPI (PD,TDI), systolic function: *S*′, TAPSE, diastolic function-*E*:*A* ratio, *E*':*A*′ ratio measured on TV**.**•PPHN: AcT:RVET, TAPSE, incompetence gradient rTV + right atrium pressure•Systemic Flow (50%): SVCO•Systemic resistance: h-PSV-half peak systolic velocity, RI-resistance index in SMA, ACA, MCA, RRA

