### Strengths of the study

3.6.

To assess the hemodynamics of the circulatory system, the authors also used echocardiographic measurements, the value of which is independent of the presence of DA, PFO, HR, age, body weight, such as the TEI index for RV and LV, and used the tissue Doppler function to assess the myocardium.

An additional advantage of the study is the large size of the study group compared to other publications.

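### TAPSE and MAPSE depend on heart size but are listed as systolic-function measures without indexing, so their case-control contrasts can be confounded by body size

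*Protocol article*

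**What the plan says.** Section 3.4.A of the protocol article names "tricuspidal annular plane systolic excursion (TAPSE), mitral annular plane systolic excursion (MAPSE") with no index, ratio or z-score. Section 3.5 gives them their role: "RV function: global RV function-MPI (PD,TDI), systolic function: *S*′, TAPSE" for the right ventricle and "systolic function-FS%, LVO, *S*′, MAPSE" for the left. TAPSE is thus one of two right ventricular systolic measures, and MAPSE one of four left ventricular ones. TAPSE also appears in the PPHN group.

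Other measures are scaled. Sections 3.4.2A and 3.4.3A express left ventricular output and SVC flow in ml/kg/min, and section 3.4.1A divides fractional shortening by the end-diastolic diameter. Section 3.6 counts as a strength the use of measures "the value of which is independent of the presence of DA, PFO, HR, age, body weight, such as the TEI index".

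Section 3.3 defines the groups. Cases are "Neonates with gestational age ≥35, who experienced an episode of perinatal ischaemia" and qualified for hypothermia. Controls are "Healthy, term neonates, who underwent echocardiography on days 3–7 of life", scanned "for reasons such as difficult adaptation, gestational diabetes of the mother etc". No matching is stated. The only size-related exclusion is SGA below the 10th centile (Table 6). That table heads its inclusion column as applying to subjects and does not say whether the exclusions also apply to controls.

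Section 5.1 makes comparison of ventricular function with the control group the leading outcome, for TH and for warming. Section 7 collects birth weight and gestational age. Section 9 describes a one-factor F test, for the power calculation.

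**The concern.** A difference in annular excursion between two groups of infants can reflect ventricular function, heart size, or both. The entry rules allow a size difference: infants of 35 and 36 weeks can appear only among the cases. The SGA exclusion is relative to gestation, so it does not close that gap. No upper weight limit is stated, and some controls are scanned because of maternal gestational diabetes. If those infants tend to be heavier (an assumption; the article does not say so), the gap widens the same way.

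The gestational-age imbalance runs one way, towards smaller cases and hence lower TAPSE and MAPSE at T1 and T2. Sections 1.1 and 1.2 lead the reader to expect that same direction from hypoxia and hypothermia. A size effect would therefore look like confirmation of the hypothesis.

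**Working it through.** **1. The plan's own figure.** The article gives 50 cases and 50 controls. It states no alpha, power, effect size or SD, so this number cannot be reproduced. It is used below only as the group size, with an assumed two-sided alpha of 0.05.

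**2. How the systolic measures are scaled.**

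| Measure | Scaling in the article |
|---|---|
| Left ventricular output | per kg (3.4.2A) |
| Fractional shortening | ratio to end-diastolic diameter (3.4.1A) |
| MAPSE, TAPSE | none stated (3.4.A, 3.5) |

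The Tei index, the global measure for both ventricles, is described as independent of age and body weight (3.6).

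**3. Illustration with a scaling law.** None of these inputs is in the article: excursion proportional to weight^(1/3), TAPSE 9 mm in the heavier group, SD 1.0 to 1.5 mm, control mean weight 3.5 kg, and no true functional difference.

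- Spurious gap = 9 × [1 − (w/3.5)^(1/3)] mm, where w is the mean weight of cases in kg.
- Standardised gap d = gap / SD.
- Rejection rate from the non-central t distribution with 98 degrees of freedom and non-centrality d × √(50/2) = 5d.

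| Case v control mean weight | Ratio | Gap (mm) | d (SD 1.5 to 1.0) | Chance of p<0.05 |
|---|---|---|---|---|
| 3.5 v 3.5 kg | 1.000 | 0 | 0 | 5% |
| 3.4 v 3.5 kg | 0.990 | 0.09 | 0.06 to 0.09 | 6 to 7% |
| 3.3 v 3.5 kg | 0.981 | 0.17 | 0.12 to 0.17 | 9 to 14% |
| 3.2 v 3.5 kg | 0.971 | 0.26 | 0.18 to 0.26 | 14 to 26% |
| 3.1 v 3.5 kg | 0.960 | 0.36 | 0.24 to 0.36 | 22 to 42% |

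**4. Cross-check without the scaling law.** Let r be the within-group correlation of size with excursion, and g the difference in mean size in SD units. Without a functional difference, the unadjusted contrast has a spurious standardised difference of r × g. Both r and g are assumptions.

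| r | g = 0.25 | g = 0.5 | g = 1.0 |
|---|---|---|---|
| 0.2 | 5.7% | 7.9% | 16.8% |
| 0.3 | 6.6% | 11.5% | 31.8% |
| 0.5 | 9.5% | 23.6% | 69.7% |

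With r = 0 or g = 0, or with a correct linear adjustment for size, the rate is 5%.

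**5. Against the study's resolution.** With 50 per group, 80% power needs a standardised difference of about (1.960 + 0.842) × √(2/50) = 0.56. The spurious differences in step 3 are 0.06 to 0.36 SD. They are smaller than that, but they add to any real effect.

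**The case against.** The strongest objection is that the article does not say the comparison is unadjusted. Section 9 is a power calculation, not the analysis model. Choice of covariates, or conversion of a listed parameter to a z-score, is commonly left to an analysis plan, and the covariates needed are collected. This stands. A reader might infer that the plan has fixed an unadjusted comparison, or that a body-size difference will be reported as ventricular dysfunction. The article supports neither: it neither specifies nor rules out adjustment, and it gives no weights from which to know that the groups differ.

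It is also fair that the magnitudes rest wholly on assumptions and fall towards 5% as the gap shrinks; that the share of controls scanned for gestational diabetes is unknown; and that the reach is limited. Fractional shortening and per-kg output are already scaled, and each ventricle also has the Tei index. The T1-to-T2 comparison within an infant is essentially unaffected by body size. Section 3.6 says only that size-independent measures were used in addition to others, not that every measure is free of size.

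What the objection does not remove is what the article itself fixes: two length measures assigned to systolic function with no scaling, in groups with different gestational-age limits and no stated matching. Collecting birth weight does not commit anyone to using it.

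**Conclusion.** The point holds as a risk of confounding in the T1 v N and T2 v N contrasts of TAPSE and MAPSE. The actual bias is unknown. Under the assumptions in step 3, group gaps of 0.2 to 0.4 kg give a false-positive rate of roughly 9 to 42% for TAPSE; groups of similar size give a rate near 5%. No separate figure was worked for MAPSE, though the same mechanism applies. The right ventricle is the more exposed, because TAPSE is one of only two systolic measures there. A reader might go further and conclude that unindexed values should never be read as systolic function. The evidence does not support that: within an infant the raw values remain interpretable, and between groups adjustment is enough.

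**What to change.** In section 3.5, state that for T1 v N and T2 v N, TAPSE and MAPSE will be adjusted for birth weight and gestational age, for example by analysis of covariance of log excursion on group, log birth weight and gestational age. Indexing the two measures to body size is the alternative. The T1-to-T2 comparison can stay in raw units.

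If cases of 35 or 36 weeks are enrolled, they have no control of the same gestation, so for them the adjustment relies on the fitted slope. The report should say so.

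The cost is wording and one or two degrees of freedom out of 98. Both covariates are already on the data collection list in section 7, so no new measurement is needed. If size explains part of the variation in excursion, residual variance will fall as well.

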Left ventricular cardiac output will be recorded from an apical 5-chamber view with a pulsed-wave (PW) Doppler with the flow volume measured in the middle of the outflow tract at the level of the ascending aorta. Aortic area will be measured in 2D echocardiography from a parasternal long-axis view. CO_LVOT_ (ml/kg/min) = velocity time integral (VTI) × aortic area × heart rate, The ECG will be recorded continuously during the examination.

3.4.3A.

Superior Vena Cava cardiac input will be recorded from subcostal coronal midsection views with a PW-Doppler with the flow volume measured in the middle of the inflow tract. SVC area will be measured in 2D echocardiography from suprasternal views. CO_svc_ (ml/kg/min) = velocity time integral (VTI) × svc area × heart rate, The ECG will be recorded continuously during the examination.

3.4.4A.

A mitral inflow velocity pattern and tricuspid inflow velocity pattern will be recorded from an apical 4-chamber view with a PW Doppler sample volume positioned at the tips of the mitral leaflets and tricuspid leaflets, respectively. Tricuspid and mitral insufficiencies will be evaluated from the measurement of the spatial distribution of the tricuspid or mitral regurgitation jet using colour Doppler examination in the apical four-chamber view. Mitral incompetence and tricuspid incompetence will be graded as trivial, mild, moderate, and severe.

3.4.5A.

The AcT/RVET ratio will be measured at the parasternal short axis view with a pulsed-wave Doppler sample volume positioned at the tips of pulmonary valve: AcT-acceleration time (time to peak velocity of pulmonary blood flow), and RVET-right ventricular ejection time.

3.4.6A.

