## Study outcomes

5.

5.1.

•Assessment of the influence of TH on systolic-diastolic functions of the left and right ventricles in comparison with the control group•Assessment of the effect of the warming phase on the systolic-diastolic functions of the left and right ventricles in comparison with the control group

5.2.

•Assessment of the influence of TH on the cerebral, visceral and renal circulation in comparison with the control group•Assessment of the effect of the warming phase on the cerebral, visceral and renal circulation in comparison with the control group

This study assesses the hemodynamic changes by means of echocardiographic Doppler examination in neonates with HIE during TH in the warming phase in comparison with the control group of healthy neonates.

The intention is to assess the impact of TH on the cardiovascular system, including the cerebral, visceral and renal circulation.

TH may have an adverse effect on the cerebral circulation by increasing vascular resistance and loss of adaptation of the cerebral vessels, which in turn can lead to hypoperfusion of vital organs.

The effect of the warming phase on the cardiovascular system by increasing heart rate and improving cardiac output will also be carefully examined. The assumption is that the changes in blood pressure (systolic/diastolic) have a decisive impact on the metabolism of drugs, including vasopressors/inotropics, which in turn affects their choice and fluid therapy.

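### Both cardiac-output formulas are labelled ml/kg/min but contain no weight term, so as written they give ml/min

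*Protocol article*

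**What the plan says.** All references are to the protocol article.

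- **Section 3.4.2A, left ventricular output:** "ml/kg/min) = velocity time integral (VTI) × aortic area × heart rate".
- **Section 3.4.3A, SVC flow:** "ml/kg/min) = velocity time integral (VTI) × svc area × heart rate".
- **Section 3.5, role of the two measures:** left ventricular output (LVO) is one of the LV systolic parameters ("systolic function-FS%, LVO"), so it falls under the primary objective in section 2.1. SVC flow is the only entry under systemic flow ("Systemic Flow (50%): SVCO") and is also named in a secondary objective in section 2.2.
- **Section 3.3, who is compared:** the hypothermia group is "Neonates with gestational age ≥35, who experienced an episode of perinatal ischaemia"; the controls are "Healthy, term neonates, who underwent echocardiography on days 3–7 of life".
- **Section 5.1, the comparison:** "Assessment of the influence of TH on systolic-diastolic functions of the left and right ventricles in comparison with the control group". A parallel outcome covers the warming phase.
- **Section 7, weight data:** birth weight is on the list of baseline data. It is the only weight listed and is not linked to either formula.
- **Section 3.6, measures described as free of body weight:** "independent of the presence of DA, PFO, HR, age, body weight, such as the TEI index for RV and LV". The Tei index is the example given; LVO and SVC flow are not mentioned there.

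**The concern.** The unit and the expression beside it contradict each other, and the same omission occurs twice. Other derived measures in section 3.4, such as fractional shortening, the tissue Doppler performance index and the resistive index, are printed with their denominators. For these two flows no correct version appears anywhere.

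An analyst who follows the printed rule gets absolute flow, which rises with infant size. The between-group outcomes compare infants enrolled from 35 weeks with term infants, and the article describes no matching on weight. A weight difference between the groups, if there is one, would then appear as a flow difference in a primary-domain LV parameter and in the sole systemic-flow measure.

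**Working it through.** **1. Units of the printed formulas.** Inputs are those named in sections 3.4.2A and 3.4.3A.

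- VTI (cm) × area (cm²) × heart rate (1/min) = cm³/min = ml/min.
- Exponents of (length, time, mass): (3, −1, 0) as written, against (3, −1, −1) for ml/kg/min.
- A different length or time unit changes only a constant factor and cannot supply the per-kg term.

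The stated unit is therefore not reproduced by either formula.

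**2. Size of the mislabelling.** The article gives no values, so these are assumed: VTI 9 cm, aortic diameter 0.75 cm, heart rate 110/min.

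- Area = π × 0.75² / 4 = 0.442 cm².
- As written: 9 × 0.442 × 110 ≈ 437 ml/min.
- Divided by weight:

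| Weight (kg) | Indexed flow (ml/kg/min) | As-written value is too large by a factor of |
|---|---|---|
| 2.5 | 175 | 2.5 |
| 3.0 | 146 | 3.0 |
| 3.5 | 125 | 3.5 |
| 4.0 | 109 | 4.0 |

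The factor is simply the weight in kg, whatever VTI, diameter and heart rate are chosen.

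**3. Carry-over into a group comparison.** Assume that every infant has the same true indexed flow, 150 ml/kg/min. The printed formula then returns 150 × weight: 375, 450, 525 and 600 ml/min at 2.5, 3.0, 3.5 and 4.0 kg. If one group averages 3.5 kg and the other is lighter by g, the spurious relative difference is g / 3.5:

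| Assumed gap g (kg) | Spurious difference |
|---|---|
| 0 | 0% |
| 0.1 | 2.9% |
| 0.2 | 5.7% |
| 0.3 | 8.6% |
| 0.5 | 14.3% |

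The assumed flow cancels, so only the ratio of mean weights matters. If the hypothermia group were the heavier one, the sign would reverse.

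**4. First against second scan in the same infant.** With one weight W per infant, the ratio of the second flow to the first is the same before and after division by W. An absolute change is scaled by W but keeps its sign. This comparison is largely unaffected.

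**The case against.** The best defence is that the unit itself states the intention. Both formulas are labelled per kilogram, birth weight is collected, and a condensed article may simply have lost the divisor. Values left undivided would also be about three times too large and would probably be noticed. Printing slips do occur nearby: in section 3.4.7A one version of the performance-index formula has lost its division sign.

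Part of this stands. Weight indexing was very likely intended, and any size artefact arises only if the formulas are used literally. The lost-text argument is weaker. The performance index is printed correctly elsewhere in section 3.4, whereas the weight term is missing from both flow formulas and appears nowhere else. Nor does the label say which weight to use.

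The defence is right about the consequence. A reader might infer that the hypothermia group will be lighter, and that its flows will therefore look falsely low in the direction expected of cooling. The article does not support that:

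- It gives no group weights. Entry from 35 weeks is a lower limit and does not show a lower mean weight, and Table 6 excludes infants small for gestational age.
- Table 1 lists reduced LVO under cooling but increased cardiac output under warming. A lighter hypothermia group would work against the expected rise at the second scan.
- The artefact cannot be set against a detectable difference, because section 9 states no standard deviation, significance level, power or effect size.

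The scope is also limited. LVO is one of several LV parameters, and no RV function parameter in section 3.5 uses either formula.

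**Conclusion.** The point holds as a contradiction between formula and unit, in both places, with nothing in the article to correct it. The unit check rests on no assumption. Applied literally, the formulas give mislabelled values, too large by a factor equal to the infant's weight in kg. They also carry any weight difference between the hypothermia group and the controls into the LVO and SVC flow comparisons.

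The amount and direction of that carry-over are unknown. The 0% to 14% range rests wholly on assumed gaps of 0 to 0.5 kg from 3.5 kg. The article does not establish that the planned comparisons are biased, or that any value already derived is wrong. It does establish that the printed rule, followed as it stands, yields the wrong quantity for a primary-domain parameter and for the only systemic-flow measure.

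**What to change.** Write both formulas, in sections 3.4.2A and 3.4.3A, as (VTI × area × heart rate) / body weight in kg, with unit ml/kg/min. Name one weight and use it consistently for all scans in both groups. Birth weight would serve, since it is already collected; what matters is that the definition does not vary between scans or groups. Check that any values already derived were divided by weight, and correct those that were not.

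The cost is one term in each of two formulas, one sentence naming the weight, and a check of the database. No new data are needed if birth weight is used, and the downside is negligible.

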### Secondary objectives

2.2.

•Assessment of cerebral circulation in neonates and controls by Doppler evaluation of blood flow in anterior cerebral artery (ACA) and middle cerebral artery (MCA), and flow in the superior vena cava (SVC) cardiac output (CO)•Assessment of visceral circulation in neonates and controls by Doppler blood flow evaluation in mesenteric artery (SMA).•Assessment of renal circulation in neonates and controls by Doppler blood flow evaluation in right renal artery (RRA).

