RV ET will be measured separately from the parasternal short-axis scan plane with a PW Doppler signal placed at the pulmonary valve annulus in the RV outflow tract. The ECG will be recorded continuously during the examination. The calculation of the Tei index (RVMPI) will be considered meaningful for the RV if the difference in heart rate for the inflow and outflow path is 5 beats/min. The isovolumetric contraction time (ICT), isovolumetric relaxation time (IRT), and ejection time (ET) will be measured, and the MPI calculated using the formula (ICT + IRT)/ET, and calculated as (*a *−* b*)*b*. Doppler echo (clicks) of the opening and closing of the aorta valve (AV) and MV will be used as reference points to estimate the timing of the ejection period.

3.4.8A.

Pulsed Doppler MPI for the left ventricle. The mitral inflow velocity pattern will be recorded from an apical 5-chamber view with a pulsed-wave Doppler sample volume placed below the mitral valve towards the ventricular septum with the PW-Doppler tracing including both the *E*/*A* (positive) and the aortic (negative) blood flow waveforms. Diastolic flow through the mitral valve in the apical five-chamber view, including early diastolic (*E*) and late diastolic, i.e., atrial (*A*) waves in m/s, will be measured with calculation of the valve *E*:*A* ratio. The ECG will be recorded continuously during the examination. The isovolumetric contraction time (ICT), isovolumetric relaxation time (IRT), and ejection time (ET) will be measured, and the MPI will be calculated using the formula: (ICT + IRT)/ET, and calculated as *a* − *b*/*b*.

3.4.B.

Doppler measurements of other organs: resistive index (RI) in RRA, SMA, ACA, MCA (11).

The resistance index has an inverse relationship with blood flow and will be calculated = (PSV − EDV)/PSV. PSV, peak systolic velocity; EDV, end-diastolic velocity. Since bradycardia can interfere with the measurement of blood flow indices: RI and PI, the authors additionally investigated half peak systolic velocity (h-PSV) deceleration time (DT) in ms, which evaluates the time that it takes a single flow velocity waveforms (FVWs) to halve its maximum systolic velocity. A perpendicular line was then drawn from the point of half the maximum velocity to the spectral waveform, which measures the deceleration time in ms (15) Figure 2.

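### The arterial outcomes (RI and half-peak deceleration time) ignore velocity amplitude, so alone they cannot support the blood-flow conclusions for SMA, RRA, ACA and MCA, and RI is not inversely related to flow in general

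*Protocol article*

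**What the plan says.** All references are to the protocol article.

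- **Secondary objectives (2.2).** The visceral objective is "Assessment of visceral circulation in neonates and controls by Doppler blood flow evaluation in mesenteric artery (SMA"). The renal objective has the same form for the right renal artery. The cerebral objective covers ACA and MCA flow and adds flow in the superior vena cava. Section 5.2 repeats the three circulations as outcomes, under TH and under warming, against controls.
- **Arterial measures (3.4.B).** RI is listed for RRA, SMA, ACA and MCA, with its meaning and formula in one sentence: "The resistance index has an inverse relationship with blood flow and will be calculated" as (PSV − EDV)/PSV. A second index is added for a heart-rate reason: "Since bradycardia can interfere with the measurement of blood flow indices: RI and PI". It is the h-PSV deceleration time in ms, "which evaluates the time that it takes a single flow velocity waveforms (FVWs) to halve its maximum systolic velocity".
- **Classification (3.5).** The arterial indices are grouped as systemic resistance. The entry names h-PSV as a velocity, followed by "RI-resistance index in SMA, ACA, MCA, RRA". SVC flow stands in a separate systemic-flow group, and LVO is under LV systolic function.
- **Expected effects.** Table 1 expects lower cerebral blood flow, vasoconstriction and lower LVO under TH. Section 5 expects raised cerebral vascular resistance and loss of vascular adaptation, "which in turn can lead to hypoperfusion of vital organs".

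**The concern.** The objectives ask about blood flow in four arteries. The indices defined for those arteries are ratios or times taken relative to the waveform's own peak, and 3.5 itself classes them as resistance. The sentence in 3.4.B joins the two by stating that RI runs inversely to flow. If that rule fails, a flow conclusion drawn from RI can be wrong in two ways: an unchanged RI may accompany reduced velocity, and a lower RI may be taken as more flow when velocity has fallen. The exposure is greatest for SMA and RRA, where nothing else is listed. Secondary outcomes are affected; the primary ventricular-function objective is not.

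**Working it through.** **Inputs from the article.** RI = (PSV − EDV)/PSV and the definition of the deceleration time (3.4.B). Figure 2 legend, SMA: PSV 83.3 cm/s, h-PSV 41.7 cm/s, deceleration time 153 ms.

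**Reproducing the article's figure.** h-PSV = 83.3/2 = 41.65 cm/s, which agrees with 41.7 to rounding. In Figure 2, then, h-PSV is a velocity and 153 ms is the separate time index.

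**Step 1: algebra, no assumptions.** Multiply the whole waveform by k.

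- RI = (k·PSV − k·EDV)/(k·PSV) = (PSV − EDV)/PSV, unchanged.
- The deceleration time solves k·v(t) = k·PSV/2, that is v(t) = PSV/2, so t is unchanged.

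**Step 2: numerical check.** Assumed shape: a sine rise over 0.06 s, then v(t) = a + (83.3 − a)·exp(−(t − 0.06)/τ), with cycle length 0.5 s and a = 15 cm/s. To match 153 ms, τ = 0.153/ln[(83.3 − 15)/(41.65 − 15)] = 0.153/0.941 = 0.163 s. End-diastolic velocity is then 19.6 cm/s.

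| k | PSV (cm/s) | EDV (cm/s) | Mean velocity (cm/s) | RI | Deceleration time (ms) |
|---|---|---|---|---|---|
| 1.0 | 83.3 | 19.6 | 40.9 | 0.765 | 153 |
| 0.7 | 58.3 | 13.7 | 28.7 | 0.765 | 153 |
| 0.6 | 50.0 | 11.7 | 24.6 | 0.765 | 153 |
| 0.3 | 25.0 | 5.9 | 12.3 | 0.765 | 153 |

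Varying a from 10 to 25 cm/s moves baseline EDV from 16.6 to 26.6 cm/s and baseline RI from 0.80 to 0.68. In no case does RI or the time move with k.

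**Step 3: falls that are not proportional** (the EDV values and the lower PSV values are assumed).

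| PSV (cm/s) | EDV (cm/s) | RI | Reading under the inverse rule |
|---|---|---|---|
| 83.3 | 15 | 68.3/83.3 = 0.82 | baseline |
| 58.3 | 10.5 | 47.8/58.3 = 0.82 | no change, although velocities are down 30% |
| 50 | 15 | 35/50 = 0.70 | more flow, although PSV is down 40% |
| 58.3 | 7 | 51.3/58.3 = 0.88 | less flow, in the right direction |

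RI therefore tracks the shape of the waveform. It responds when EDV falls more than PSV, as with raised resistance, but it does not track flow in general.

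**Step 4: does the second index repair this?** Take the same a = 15 waveform and lengthen the cycle from 0.45 to 0.60 s. RI rises from 0.746 to 0.790 and the deceleration time stays at 153 ms. The added index thus meets its stated purpose of avoiding the heart-rate effect. Steps 1 and 2 show that it does nothing for loss of amplitude.

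**Step 5: what does scale with velocity?** PSV, EDV and mean velocity do. So does SVC flow (VTI × SVC area × heart rate, 3.4.3A): with area and heart rate unchanged it falls to 70% or 60% of baseline at k = 0.7 or 0.6. LVO is built the same way (3.4.2A). None of the arterial velocities is listed in 3.5 as an outcome, unless its h-PSV entry is read literally as a velocity; even then it is filed under resistance.

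**The case against.** The strongest case on the other side has five parts.

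1. **The cerebral objective has a flow measure.** SVC flow is volumetric, in ml/kg/min. This stands. It is not specific to the brain, and 3.5 files it as systemic flow, but the cerebral objective does not rest on RI and deceleration time alone.
2. **A fall in output is measured directly.** LVO is an outcome, so RI would be read beside it. This stands in part: LVO shows that total output fell, not how the mesenteric or renal share changed.
3. **The stated hypothesis is resistance first.** Section 5 expects raised cerebral vascular resistance, and Table 1 lists vasoconstriction and redistribution. RI suits such changes, and an exactly proportional fall is a special case. This stands, and it is why RI should be kept.
4. **Velocity is not flow either.** Without vessel diameter, and with vasoconstriction expected, velocity may hold or rise while flow falls. This stands and limits the remedy.
5. **An article condenses the full plan.** Which derived variables are tabulated may be set out elsewhere, and PSV and EDV must be read anyway. This is fair for the missing list of velocities. It does not excuse the unconditional sentence in 3.4.B, or the mismatch between flow in 2.2 and resistance in 3.5, because the article states both.

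A reader might go further and infer that the study would miss any fall in organ perfusion, or would detect one no more often than chance. The documents do not support that. Blindness is exact only for a proportional fall, and the article gives no between-infant variability from which to calculate a detection probability. A reader might also infer that the authors will report an unchanged RI as preserved flow. The article never says so; its inverse rule merely permits it.

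**Conclusion.** The point holds in a limited form. RI and the deceleration time are exactly unchanged by a proportional fall of any size, and RI can move opposite to the stated rule (0.82 to 0.70 in the example). The unconditional inverse relationship in 3.4.B is therefore wrong in general. For SMA and RRA, where no other outcome is listed, and for the ACA/MCA part of the cerebral objective, these indices alone cannot support a conclusion about blood flow. They can support one about resistance or pulsatility.

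The invariance is algebra and needs no assumption. The worked values rest on an assumed waveform shape, cycle length and diastolic velocities; only PSV 83.3, h-PSV 41.7 and 153 ms come from the article. Whether TH produces a near-proportional fall in these arteries cannot be settled from the document.

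Sections 3.4.B and 3.5 also disagree on h-PSV: a time in one, a velocity in the other. The two readings behave differently, since half of PSV scales with amplitude and the time does not.

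**What to change.** - **3.4.B and 3.5:** add PSV and EDV as reported outcomes for ACA, MCA, SMA and RRA and, where the stored trace allows, time-averaged mean velocity. Record the insonation angle. Call them velocity surrogates, not volumetric flow, because no diameter is listed for these arteries and TH may cause vasoconstriction.
- **3.4.B:** delete the inverse-relationship statement or restrict it to the conditions under which it holds. Interpret RI and deceleration time as resistance or pulsatility indices only, alongside LVO and SVC flow.
- **2.2 and 5.2:** bring the wording into line, so that conclusions from RI and deceleration time are stated as resistance.
- **3.4.B and 3.5:** state whether h-PSV means the deceleration time in ms or the velocity, and use one term throughout.

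The cost is protocol wording and a few extra data fields per trace. PSV and EDV are already read to obtain RI, and the scans are saved for offline measurement (3.4). The downside is that velocities depend on the insonation angle and are noisier than RI, from which a common angle error cancels.
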